## Abstract

**Background:**

Pregnancy, and childbirth can encounter many challenges for the teen mother, family, and health system. The simultaneity of two transition periods, i.e. transition to adulthood and post-partum period may disrupt the acceptance of new roles. Lack of knowledge, information and life skills in managing this situation may threaten the physical and mental health of the mother, and child, as well as reduce the level of role adaptation. One way to increase women's empowerment in postpartum care is self-efficacy promotion training program. The current mixed methods study will be conducted to provide an interventional program sensitive to the culture of the Iranian society for adolescent mothers to improve their self-efficacy.

**Method:**

This study will be conducted as an exploratory sequential mixed methods study (Qual-quan) based on a pragmatism paradigm in four phases. In the first phase, a qualitative study will be performed using a directed content analysis method to explore the needs and strategies related to promote postpartum self-efficacy from the viewpoint of teen mothers, their family, healthcare providers, and policymakers. In the second phase, using a scoping review, self-efficacy promotion strategies, and postpartum care service packages, programs, guidelines, and protocols in other countries will be identified. In the third phase, with integrating the results of qualitative phase and scoping review, the first draft of program will be developed, and validated by an expert panel based on the Delphi approach in three rounds. In the last step, the effectiveness of the interventional program will be evaluated on postpartum self-efficacy of teen mother.

**Discussion:**

Developing an interventional program that includes teen mother’s experiences, evidence based practice principles, and health staff opinions in a distinct cultural and social context can supply new direction to lead manager, policymakers, and other health care provider to improve the maternal self-efficacy in infant, family, and self-care with considering their age characteristics.

## Introduction

Adolescence as a transition period is considered one of the most sensitive life stages for adolescents and their families [1]. Upon entering this period, they experience rapid physical, cognitive, psychological, and social growths that can influence their feelings, thinking, decision-making, and their interactions with the world around them [2]. Since the transition from childhood to adolescence is associated with many psycho-social pressures; any additional stress such as early marriage, pregnancy, childbirth, and adaptation to motherhood roles can double the burden of psycho-social pressure imposed on them and as a result interfere with their roles as a daughter, student, wives and mothers, as well as affect their relationships with peers, family, and society [4].

Investing in the health of adolescents is also important from a demographic rationale. Adolescents make up a fifth of the world’s population, and 85% of them live in developing countries [6]. It is estimated that about 12 million girls aged 15–19 years and at least 777,000 girls under 15 years give birth annually in developing countries; which in most cases (at least 10 million) is unplanned. Also, the average global birth rate per 1000 women aged 15–19 is 65, this number in Iran is 40.81 birth [7]. It is predicted that the trend of teen pregnancy in the world will increase and reach at least 1.15 million by 2030 [8].

Adolescents make up about a fifth of Iran’s population, and according to the report of the Iran Statistics Center, and Office of Women’s Studies and Research in 2016, the marriage of men aged 20–24 to women aged 15–19 accounted for the largest number of registered marriages. Also, only 33 percent of them used contraceptive methods and one-third of them got pregnant in the first year after marriage [9].

Pregnancy and childbirth in this age group are important issues that can threaten their physical and mental health, and increase the risk of mother and child death [10]. The World Health Organization (WHO) mentions teen pregnancy as the number one killer of adolescents; worldwide, one out of every 3900 teen girls dies from the consequences of pregnancy and childbirth, and in developing countries, this number is 250 [11].

In addition to the negative physical/psychological consequences of teen pregnancy, adolescents are particularly vulnerable to postpartum changes. Transition to the postpartum period and accepting a new baby, as well as adaption to parental roles, can be a stressful experience for all parents, regardless of age and childbearing background, and requires adaptation to the upcoming changes [13].

Teen mothers are more confused in accepting multiple roles, because in addition to the underlying factors of teen pregnancy (e.g., poverty and low socioeconomic level), the normative changes that occur during adolescence such as the formation of individual identity, tendency to authority, and also the inability to negotiate in one’s relationships with the family and others can be a big obstacle in adapting to the parental role [14].

Due to the importance of the postpartum period in mother and child health, many international guidelines (e.g., NICE, WHO, and ACOG guidelines) have been developed for better postpartum care [17–20]. The main approach of all existing guides is to provide services and health promotion and does not pay attention to improving the self-efficacy and empowerment of mothers in the postpartum cares. Moreover, the content of care for all mothers with different characteristics and in all age groups was similar to a large extent.

The results of various studies indicate that the postpartum period of teen mothers should be viewed differently. Various studies have proposed postpartum care in the form of youth-friendly services, school-based postpartum care, home visit, web-based care, and group care models, and the nature of all models is women empowerment [21–25]. From the perspective of the WHO, empowerment as the heart of health promotion is a process through which people gain more control over decisions and activities affecting their health. One way to increase women’s empowerment is self-efficacy promotion training program [26, 27].

Self-efficacy is considered a fundamental concept in maternal care because it emphasizes the importance of self-management and empowerment [28]. Bandura’s self-efficacy theory states that people generally take action if they believe that they can do something, and if they believe that they will fail in doing something, they avoid it [29]. Self-efficacy promotion requires four main resources, including successful experiences of the individual, social modeling, social persuasion, and psychological responses, which should be considered when designing interventions [30].

Adolescents, due to their age characteristics, need to receive their information and special care, most of which is not provided in the current health system designed for adults. Therefore, the provided services should be sensitive and consistent with their biological, psychosocial, and cognitive needs. Thus, the existence of a comprehensive program to consider all aspects of adolescents' characteristics, and their needs, under the socio-cultural, and health structure of Iranian society, seems to be essential. Therefore, the current study is designed to develop a program for improving the self-efficacy of adolescent mothers in child, and herself cares during the postpartum period, using a sequential exploratory mixed method study.

### Objectives

The objectives of the four stages of the study are as follows:

#### The first phase: qualitative study

1.1.Identifying the needs and strategies for self-efficacy promotion of teen mothers in child, and herself cares during the postpartum period, from the perspective of the teen mother, health care providers, managers, and policy-makers with a directed content analysis approach.

#### The second phase: scoping review

Determining postpartum care service packages, programs, guidelines, and protocols in the other countries.Extracting postpartum self-efficacy promotion strategies and recommendations from the literature.

#### The third phase: designing a postpartum self-efficacy promotion program

Designing the initial self-efficacy promotion program for teen mother by integrating the results of qualitative phase and scoping review.Validating the developed postpartum self-efficacy program for teen mothers by expert panel.

#### The fourth phase: implementation of the postpartum self-efficacy promotion program for teen mothers

1.1.Determining the effect of a comprehensive postpartum self-efficacy promotion program on the self-efficacy score of teen mothers**.**

## Materials and methods

The current study will be conducted as an exploratory sequential mixed methods study (Qual-quan) based on a pragmatism paradigm in four phases. In the first phase, a qualitative study will be performed and the conclusion resulting will be analyzed using a directed content analysis method to determine the needs and strategies related to promoting postpartum self-efficacy of adolescent mothers in infants and herself cares from the viewpoint of teen mothers, their family, healthcare providers, and policymakers. Data will be collected via semi-structured individual in-depth interviews and taking field notes. Participants who are eligible for participation will be selected in a purposive approach and with maximum variation. Sampling will be continued until data saturation. In the second phase, using a scoping review, self-efficacy promotion strategies, and postpartum care service packages, programs, guidelines, and protocols in other countries will be identified. In the third phase, the results of the qualitative phase, in addition to the scoping reviews, will be used to design an appropriate interventional program. Then, this proposed program will be validated by an expert panel including obstetricians, midwives, and reproductive health professionals based on the Delphi approach in two, or three rounds, and then according to expert opinions, a comprehensive postpartum self-efficacy program will be developed for teen mothers. In the last step, the effectiveness of the interventional program is evaluated on postpartum self-efficacy. The collected data will be entered into SPSS statistical software version 22 and will be analyzed by descriptive-analytical statistics.

### Phase I: qualitative study

At this phase, the researcher is trying to explore the needs, barriers and strategies for self-efficacy promotion of teen mothers in the postpartum period to design an interventional program for their participation. This study will be carried out using a directed content analysis method based on Bandura’s self-efficacy theory.

### Study participation

In the qualitative part of the current study, participants will include adolescence mother aged between 15 and 19 years with the maximum variation of the age, mode of delivery, gravidity, time elapsed since delivery, social class, economic status, residency, and educational level. Also, health service providers who have experience in providing health care and treatment services to teen mothers including gynecologists, reproductive health specialists, general practitioners, midwives, psychiatrists, psychologists, family health experts, social workers, as well as, maternal health policy makers, with at least two years of working experience in this field, would be recruited for the study with informed consent.

In order to access the teen mothers, after obtaining the necessary permits, they will be contacted using the Sib system, which records information on the mothers’ pregnancy, delivery, and postpartum care, as well as the mothers’ contact numbers and addresses. After explaining the objectives of the study, we ask them to participate in our study. Also, in the health care centers that had more teen mothers, their health care providers will also be interviewed.

### Research environment

The interviews will be performed in coordination with the participants' views at the time and place of the participants’ desire including hospital, health care centers, midwifery or gynecologists’ offices, deputy of health and medical centers, work places, home, university, etc.

### Sampling method

Participants will select through purposive sampling, and the interviews will conduct with those who had the inclusion criteria after receiving their informed consent. The interviews will be continued until data saturation, and it will stop if data saturation occurs.

### Inclusion criteria for teen mother

Willingness to participate in the study, and providing the informed consentAge between 15 and 19 yearsThe elapsed time from childbirth between 42 days to one yearHaving a healthy infant without any congenital disordersIranian NationalityNot history of well-known psychiatric disorder requiring medicationBeing able to participate in the interview physically or mentally

### Inclusion criteria for health care provider

Having at least 2 years of working experience in healthcare centers for healthcare providers, and 3 years for policymakers, which are all in the field of providing services to teen mothers.willingness to participate in the study with informed consent

### Data collection process

After approving the protocol of study by the ethics committee of Isfahan University of Medical Sciences (IR.MUI.NUREMA.REC.1401.112), and taking the necessary permissions, the researchers will select the participants by referring to the research environment. After providing complete explanations regarding the purpose of the study and the method of research, the eligible participants are assigned an appointment in a private and comfortable environment. All participants will ensure that their participation is voluntary, and they are free to discontinue their cooperation whenever they want. After obtaining verbal and written consent, the interviews will be recorded by an MP4 device. In cases where voice recording is not permitted, the interviews will be done by taking notes.

In a face-to-face meeting, data will gather through individual, in-depth, and semi-structured interviews along with taking notes in the field**.** In this method, the first several interviews will be conducted to get familiar with possible and unpredicted issues, as well as guide for subsequent interviews.

The interview guiding questions will consist of open-ended questions based on the main constructs of Bandura’s self-efficacy theory that researcher wants covered in the interview. Directed questions guide how to conduct the interview. In this study, Interviews begin with the guiding questions “How is the experience of motherhood? How much do you manage to take care of yourself and baby?” and “What problems do you have about taking care of yourself, and your baby? What is difficult for you to do? How do you cope with your situation?” and “How do your husband and family take care of you? How much do they give you the feeling that you can handle your situation?”. The directed question for assessing “social modeling” construct will be asked in the form of “can seeing the success of teen mothers like you motivate and stimulate you to do these things too?” or “How do teen mothers take care of their children? Do you think you are like them or more successful than them?”.

Moreover, the following question “Has anyone told you that you can’t do something? or will they tell you that you are more successful in a certain field? What do you do very well in taking care of your child that others tell you?” will be asked for evaluating the successful personal experiences, and social persuasion constructs.

And the questions which asked from health care provider and maternal health policy makers include: “From your point of view, what factors can affect a teen mother’s belief in her ability to manage and adapt to the parental role? Is there a difference between teenage and adult mothers in this regard?” or “what is your challenge in the care of teen mothers? which kind of problems will the care givers be encountered in the care of teen mothers and what are your suggestion?” and “What can be done in order for teen mothers to be able to cope, and manage their needs, and condition? What interventions are more appropriate? Why?”.

What solutions can you offer in order for teen mothers to be able to cope with their work?

The length of the interview will be adjusted according to the willingness of the participant to answer the questions. If needed, a supplementary interview will also be scheduled. After the end of each session, the audio file of the interview will be transcribed immediately, and data analysis will be performed simultaneously with data collection. Data collection will continue until the data saturation, that is when no new code or data is extracted.

### Data management and analysis

Data analysis and interpretation will be deductively done using directed content analysis introduced by Hsieh & Shannon [31]. The existing previous theory or conceptual framework with principal concepts or constructs can provide predictions about the relationships between variables, therefore will assist with the organization and coding of data. In this approach, the previous theory can be validated, and probably expanded and strengthened. The bandura self-efficacy theory will be used to assist with organization and coding of data.

The three main stages, including preparation, organization, and reporting will be applied for directed content analysis. The first phase will begin with carefully reading the whole text, and selecting the unit of meanings. Moreover, the researcher will try to obtain a sense from the whole data and understand “what’s going on”. The organization stage is the development of an unconstrained classification matrix and data coding based on the categorize of model. In this step, similar meaning units will be placed in the constructs of Bandura’s self-efficacy model (successful experiences of the individual, psychological responses, social modeling, and social persuasion). Any section of the text that cannot be categorized by the initial coding scheme will be assigned a new code. In the reporting phase, the researcher will create a link between the results and describe the analysis process in detail. The Max-QDA version 10 software will be used to facilitate, organization and analysis of the qualitative data.

### Rigor and trustworthiness

To assure the rigor, and trustworthiness of the findings, four criteria of Lincoln and Guba, including credibility, dependability, confirmability, and transferability, will apply as the scientific accuracy criteria [32, 33]. In order for credibility, different methods including the member-checking technique (review by the participants), the maximum variation in the participant' selection, in-depth interviews at different times and locations, constant engagement with the research subject, and integrating various data-gathering methods (e.g., individual interviews, focus group discussions, daily notes, and field notes) will be used. The dependability of the findings will be ensured through accurate documentation and recording research details. To guarantee the data confirmability, the external observer’s method will be used to control the accuracy of the coding and theme extraction process and find any contradictory cases. To enhance the transferability, the results will be offered to some women with similar characteristics to the participants, who were not present in the research to judge, and compare the similarity of the findings with their own experiences.

### Second phase: scoping review

In this phase, the postpartum care service packages, programs, guidelines, and protocols, as well as recommendation, strategies, and interventions for postpartum self-efficacy of adolescent mother will be extracted using a scoping review methodology. Using this method enables combining a wide range of studies and summarizing information from a variety of sources and evidence to gain a comprehensive understanding of a given field of study, as well as, inform future research. The 5-step framework developed by the Joanna Briggs Institute will be used for this scoping review [34, 35].

### First step: identify the research question

In the first step, the research question will be identified. The primary questions are “What is the current body of scientific literature regarding the various strategies for promoting adolescence mother self-efficacy”, and “what is the main challenges, and need of adolescence mother in postpartum period”.

### Step 2: identify relevant studies

In the next step, the relevant studies will be identified. For this stage, the original articles published in English and Persian electronic databases including PubMed, Scopus, Embase, Web of Science, Cochrane Database of Systematic Reviews (CDSR), Sid, IRANDOC, and Mag-Iran will be systematically searched for the period up to 30 January 2023 using the following search strategies in accordance with the Mesh browser keywords and free-text words: (((Adolescent[mh] OR Adolescents[tiab] OR Adolescence[tiab] OR Teens[tiab] OR Teen[tiab] OR Teenagers[tiab] OR Teenager[tiab] OR Youth[tiab] OR Youths[tiab] OR Adolescents, Female[tiab] OR Adolescent, Female[tiab] OR Female Adolescent[tiab] OR Female Adolescents[tiab] OR Minor[tiab]) AND (Self-efficacy[mh] OR confidence[tiab] OR self-concept[mh] OR competence[tiab] OR self-confidence[tiab] OR self-perception[tiab] OR confidence[tiab])) AND (Program[mh] OR education program[tiab] OR guideline[tiab] OR service package[tiab] OR protocol[tiab] OR Intervention[tiab] OR health education[tiab] OR client education[tiab] OR women education[tiab] OR Antenatal education[tiab] OR perinatal education[tiab] OR Clinical Trial[mh] OR Evaluation Study[mh] OR Controlled Clinical Trial[tiab] OR Randomized Controlled Trial + [tiab] OR Adaptive Clinical Trial[tiab] OR control*[tiab] OR random*[tiab] OR trial*[tiab] OR effectiveness[tiab] OR efficacy[tiab] OR compar*[tiab] OR clinical*[tiab] OR experiment*[tiab] OR impact evaluation[tiab] OR impact study[tiab] OR impact assessment[tiab] OR outcome evaluation[tiab] OR out-come study[tiab] OR outcome assessment[tiab])) AND (Postpartum Period[mh] OR Postpartum[tiab] OR Postpartum Women[tiab] OR puerperium[tiab] OR Child[tiab] OR newborn[tiab] OR infant[mh] OR infancy[tiab] OR parent[tiab] OR mother[tiab] OR pregnancy[mh] OR post-natal[tiab] OR neonate[tiab] OR neonatal[tiab]). In addition, hand-searching in gray literature databases (e.g., Google Scholar, Global Index Medicus (GIM), Open Grey SIGLE, World Cat, NTIS, UW Libraries Search) and screening reference lists of eligible articles will be used to find more relevant records. All type of articles including quantitative, qualitative, and mixed methods studies will be assessed. The Endnote software ver.X9 will be used for omitting duplicate studies in different databases.

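### The scoping-review search string has no free-text term for self-efficacy, so a record that names the concept only by that word meets the self-efficacy block only through MeSH indexing

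*Protocol article*

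**What the plan says.** The first review question (First step: identify the research question) is "What is the current body of scientific literature regarding the various strategies for promoting adolescence mother self-efficacy". Step 2 says the string was built from MeSH keywords and free-text words, and prints it in full. It has four blocks joined by AND: population, self-efficacy, programme or study design, and postpartum/mother/infant. A record must satisfy all four.

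- **Self-efficacy block:** "Self-efficacy[mh] OR confidence[tiab] OR self-concept[mh] OR competence[tiab] OR self-confidence[tiab] OR self-perception[tiab] OR confidence[tiab".
- **Population block:** it opens with "Adolescent[mh] OR Adolescents[tiab] OR Adolescence[tiab] OR Teens[tiab] OR Teen[tiab] OR Teenagers[tiab] OR Teenager[tiab] OR Youth[tiab] OR Youths[tiab" and closes with "Adolescents, Female[tiab] OR Adolescent, Female[tiab] OR Female Adolescent[tiab] OR Female Adolescents[tiab] OR Minor[tiab".
- **Postpartum/mother/infant block:** it includes "infant[mh] OR infancy[tiab] OR parent[tiab] OR mother[tiab] OR pregnancy[mh] OR post-natal[tiab".
- **Programme/design block:** it includes "effectiveness[tiab] OR efficacy[tiab] OR compar*[tiab] OR clinical*[tiab] OR experiment*[tiab".

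Step 2 also plans hand-searching of gray literature sources, Google Scholar among them, and screening of the reference lists of eligible articles. The database search runs to 30 January 2023.

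**The concern.** The word on which the whole review turns has a heading tag but no title-and-abstract tag, while a looser neighbour, `confidence[tiab]`, is entered twice in the same block. That looks like a drafting slip, and it departs from the stated intention to use both kinds of term. The population and mother/infant blocks have smaller gaps of the same kind: the word forms that occur in phrases such as 'adolescent mothers', 'teenage mothers' and 'maternal' are not there as stand-alone free text.

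Because the blocks are joined by AND, failing one of them is enough to lose a record. The records at risk are those that use the protocol's own vocabulary and have no MeSH indexing to fall back on. The review's results are combined with the interviews to design the programme (third phase), and they help to define the areas of self-efficacy studied in phase four (Study variables). A less sensitive search therefore weakens one of the inputs to the intervention.

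**Working it through.** The document gives no figure to reproduce, so the check is a literal reading of the printed string. `[mh]` is taken as a MeSH heading and `[tiab]` as a word or phrase in the title or abstract, with `*` as truncation.

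**Step 1. Entries per block, counted from Step 2.**

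| Block | Entries | Free text | MeSH |
|---|---|---|---|
| Population | 14 | 13 | 1 (adolescent) |
| Self-efficacy | 7 | 5 | 2 (self-efficacy, self-concept) |
| Programme/design | 30 | 27 | 3 |
| Postpartum/mother/infant | 14 | 11 | 3 (postpartum period, infant, pregnancy) |

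The five free-text entries in the self-efficacy block contain only 5 − 1 = 4 different terms, because `confidence` is repeated: confidence, competence, self-confidence and self-perception.

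**Step 2. Look up each key word as a stand-alone free-text term.**

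| Word | Stand-alone `[tiab]`? | Where it does occur |
|---|---|---|
| self-efficacy | no | `[mh]` only |
| adolescent | no | `[mh]`, and inside two free-text phrases with 'Female' |
| teenage | no | nowhere |
| mothers | no | nowhere (`mother[tiab]` is present) |
| maternal | no | nowhere |
| infant | no | `[mh]` only |
| postnatal | no | only as the hyphenated `post-natal[tiab]` |

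`efficacy[tiab]` is in the string, but in the programme/design block. That block is ANDed with the self-efficacy block, so a match there cannot stand in for a match in the other.

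**Step 3. Match constructed texts against the free-text terms alone.**

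| Constructed text | Population | Self-efficacy | Design | Mother/infant |
|---|---|---|---|---|
| (a) 'maternal self-efficacy in adolescent mothers' | none | none | efficacy | none |
| (b) 'maternal self-efficacy in teenage mothers: a trial; self-efficacy postpartum in adolescents' | adolescents | none | trial*, efficacy | postpartum |
| (c) 'Effect of an intervention on maternal self-efficacy in adolescent mothers. Adolescents had higher parenting confidence postpartum.' | adolescents | confidence | intervention, efficacy | postpartum |

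Text (a) fails three of the four required blocks. Text (b) isolates the main fault: it passes the other three blocks and is lost on the self-efficacy block alone, although it uses the word self-efficacy twice. Text (c) passes all four, because it happens to carry a listed synonym wherever one is needed.

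**The case against.** A reader might infer that any paper on self-efficacy in adolescent mothers can be found only through MeSH. The document does not support that. The string has free-text adolescents, adolescence, teen, teenager, youth, competence, confidence, child, mother, parent, newborn and postpartum, and an abstract with one suitable word in each block is retrieved, as text (c) shows. `[tiab]` covers the abstract as well as the title, so a test on short titles made of the missing words is a worst case and not an estimate of retrieval. Nor is adolescent wholly absent as free text: it occurs in two phrases with 'Female', although neither matches 'adolescent mothers'.

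Bare `confidence[tiab]` also matches 'confidence interval'. That adds irrelevant records, but it lets some quantitative self-efficacy papers through the block by accident, so part of the cost is extra screening and not lost studies.

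A second tempting reading is that this PubMed-style string is run unchanged in Scopus, Web of Science and the Persian databases, where MeSH tags might not work. Step 2 prints one string for all eight databases but does not say that it is used without adaptation, and a condensed article may leave such adaptations to a fuller document. That claim is not made here.

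The safeguards in Step 2 are real. The review is also one input among several: the programme draws on interviews and an expert panel too, and the questionnaire (Data collection method) rests on interviews and a search of existing questionnaires.

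These points limit the size of the problem. They do not explain why the key term has no free-text entry in a string that is meant to have both kinds, and that string is printed in full, so this is not detail left to another document.

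**Conclusion.** The point stands in a limited form. A record that names the concept only as self-efficacy satisfies the self-efficacy block only through MeSH indexing. A record that relies on adolescent, teenage, mothers, maternal or infant, with no listed synonym in the block concerned, is missed by the free-text part of the string in the same way. Run as printed, the search is less sensitive than intended for its own key concept.

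The number of records lost cannot be computed from the document. It depends on how many relevant records lack indexing, how many abstracts carry a listed synonym, and how much the hand-search and reference lists recover. The conclusion assumes literal matching of the printed terms; how each database treats plurals and hyphens is not stated. It bears on the completeness of the phase two review and not on the phase four comparison or its statistics. It is a modest fault that is cheap to correct.

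**What to change.** In the self-efficacy block, replace the second `confidence[tiab]` with `self-efficacy[tiab]` OR the two-word phrase `self efficacy[tiab]`. Keep the first `confidence[tiab]` as it is: narrowing it to phrases such as 'maternal confidence' would reduce noise but could lose abstracts that word the idea differently.

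In the population block, add `adolescent[tiab]` and `teenage[tiab]`. In the postpartum/mother/infant block, add `mothers[tiab]`, `maternal[tiab]`, `infant[tiab]` and `postnatal[tiab]`. Then rerun the search to the same cut-off date of 30 January 2023, so that only the terms change.

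The cost is a few hours to revise and rerun, plus more records to screen.
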